#### 2.7.2. Secondary outcomes

Other cognitive domain examinations and LTP-like cortical plasticity will also be measured. Overall cognitive function will be assessed using scores from the Montreal Cognitive Assessment Test (MOCA) as well as the Mini-Mental State Examination (MMSE). In addition, the Wechsler Memory Scale -Logical Memory Test (WMS-LM) and digit span test (DST) will be used to assess memory function and attention, respectively. Language function is measured using the scores of the Animal Fluency test (AFT) and Boston Naming Test China version (BNT-C) test. Measures of executive function include the symbol digitized modality test (SDMT) and the trail making test (TMT) parts A and B (Zhong et al., 2021). Time to completion of TMT A and TMT B will be logged and analyzed. In addition, all participants will be asked to complete two computer experiments conducted using E-Prime 2.0 software (Psychology Software Tools Inc., Pittsburgh, PA, United States). The n-back (*n* = 1) task is used to evaluate working memory, while the Go/No-Go task is used to assess inhibitory control ability (Borgwardt et al., 2008; Kumar et al., 2017). The accuracy and response time will be recorded.

The changes of the MEP amplitude will be measured to assess LTP-like cortical plasticity. Twenty consecutive MEPs of 5-s intervals will be evoked by single-pulse TMS at the left motor hotspot of 120% RMT intensity, and the peak-to-peak average value recorded. The whole LTP-like plasticity assessment includes five time points, whereby two baselines before and 5, 10, and 30 min after the intermittent theta burst stimulation (iTBS) protocol. Two baseline measurements are performed 10 min apart, and the subsequent iTBS paradigm is applied if the variation between the two average measurements is < 15%. The iTBS protocol consists of a burst of three stimuli at 50 Hz and repeated at 5 Hz. A 2-s train of this protocol will be repeated every 10 s for a total of 192 s (600 pulses) with 80% RMT over the left hotspot (Huang et al., 2005; Yu et al., 2020).

### 2.8. Data analysis

SPSS V.23.0 will be used to analyze the data, and levels of statistical significance will be set at *p* < 0.05. For descriptive statistics, the Shapiro–Wilk test will be applied to check for normal probability prior to data entry. Data from the normal distribution will be reported as mean and standard deviation, whereas medians with interquartile ranges will be used to express the non-normal distribution. Categorical variables will be described as frequency as a function of percent. Demographic characteristics and baseline variables will be compared between the two groups using independent samples *t*-test or non-parametric Mann–Whitney test for continuous data, and comparisons of categorical variables using chi square or Fisher’s exact tests. Based on the existing literature, we can determine whether the unbalanced baseline data affect the results and, if so, conduct covariance analysis using the baseline data as covariates to control for the effect of potential confounders. The experiment will be analyzed using intention-to-treat (ITT) and missing data will be interpolated using multiple imputation method.

For normally distributed data, a repeated-measures analysis of variance (ANOVA) will be conducted to evaluate changes in treatment effect between and within groups (group: real vs. sham rTMS) (time: pre-vs. post-treatment). Alternatively, for non-normally distributed variables, we will perform the Wilcoxon signed rank test for within group comparisons, and the Mann–Whitney test will be applied to compare the effect between groups at each time point. In addition, we also aim to use a repeated-measures ANOVA to examine LTP-like plasticity as a function of percent change at four time points (last baseline, 5, 10, and 30 min after iTBS) between the two groups. *Post hoc* comparisons between groups will be used using the Bonferroni correction method. The generalized linear model (GLM) will be considered if the data is not normally distributed. To investigate the relationship between brain measurements and clinical cognitive function characteristics, we will perform correlation analyses by repeated measures linear regressions.

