### 2.4. Sample size

According to Jia et al. (2021), the sample size was calculated using G*Power software, with a Cohen’s effect size of *d* = 0.7979 for rTMS on the 12-word Philadelphia Verbal Learning Test as the primary outcome (Jia et al., 2021). Moreover, alpha and power are set at 0.05 and 80%, respectively. Our study will increase the inclusion number by 10% to compensate for possible patient shedding. The final number of participants will be 30 per group.

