### 2.5. Randomization and blinding

The randomization procedure will be performed by a researcher at a 1:1 balanced distribution ratio of (real or sham group) using a web-based randomization tool.^1^ Randomization information will be passed by sealed envelope until completion of the study. One investigator will oversee the random sequence and, at the intervention stage, the trained investigator will set the mode of the stimulus (real or sham group) according to the number on the paper in the envelope. Participants will be identified by codes rather than real names throughout the study. The neuroelectrophysiological assessor and the statistician will be blinded, as they are independently involved in the assessment or data analysis process, respectively.

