### 2.7. Outcome measurements

#### 2.7.1. Primary outcomes

The Auditory Verbal Learning Test-Huashan version (AVLT-H) assessment will be used as the primary outcome to assess EM for our study. The AVLT-H assesses several aspects of verbal EM through a list of 12 words, such as short or long-term delayed recall and recognition. It has been widely used as a semantic categorization memory test in mainland Chinese populations (Li et al., 2016). The AVLT-H scores include AVLT-H immediate recall total score (AVLT-H-IR-S), AVLT-H short-term delayed recall score (AVLT-H-SR-S) with a 5-min delay time, AVLT-H long-term delayed recall score (AVLT-H-LR-S) with a 20-min delay time, AVLT-H total, and AVLT-H recognition score (AVLT-H-REC-S) (Zhao et al., 2012). This test has been proved to be a sensitive diagnostic evaluation of cognitive impairment (Li et al., 2016).

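### Adjustment for the T0 AVLT-H score should be fixed in advance (ANCOVA) instead of depending on how baseline imbalance is read; a free gain in precision

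*Protocol article*

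**What the plan says.** In section 2.7.1 the AVLT-H "assessment will be used as the primary outcome to assess EM for our study". Five scores are listed under it: immediate recall, short-delay recall, long-delay recall, total and recognition. Outcomes are measured twice, at T0 before treatment and at T1 at its end.

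Section 2.8 then sets out these steps:

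- Baseline variables are compared between arms by t-test or Mann–Whitney test (chi-square or Fisher for categories).
- With an appeal to published literature, "we can determine whether the unbalanced baseline data affect the results and, if so, conduct covariance analysis using the baseline data as covariates". The stated aim is to control possible confounding. There is no threshold for imbalance, no list of covariates and no rule for the decision.
- For normally distributed outcomes, "a repeated-measures analysis of variance (ANOVA) will be conducted to evaluate changes in treatment effect between and within groups", with arm and pre/post time as the factors.
- Outcomes that are not normal go to signed-rank tests within arms and Mann–Whitney tests between arms at each time point, without baseline adjustment.
- The analysis is by intention to treat, with multiple imputation of missing data.

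**The concern.** Every participant has a T0 score, so adjusting for it costs nothing. Its value does not depend on the arms looking unequal: in a randomised trial, adjustment for a prognostic baseline removes outcome variation whether or not a chance imbalance occurred. The plan instead makes the less efficient test the default and leaves adjustment to a discretionary decision taken once the baseline data have been seen.

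Two things are at stake. One is precision, in a trial of only 60 people. The other is that two candidate models exist for the primary outcome, they can disagree on significance, and nothing written says which one governs.

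**Working it through.** **Inputs.** From section 2.4: "effect size of *d* = 0.7979 for rTMS on the 12-word Philadelphia Verbal Learning Test as the primary outcome"; "alpha and power are set at 0.05 and 80%, respectively"; an allowance to "increase the inclusion number by 10% to compensate for possible patient shedding"; and "The final number of participants will be 30 per group". Allocation is 1:1 (section 2.5). The article gives neither rho (the T0–T1 correlation) nor the scale of d (post score or change), so both are treated as assumptions and varied.

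**1. The plan's own figure.** A two-sided two-sample t-test with d = 0.7979, alpha 0.05 and 80% power needs 26 per arm (power 0.805). Then 26/0.9 = 28.9, so 29 per arm, against 30 stated. The sample size reproduces to within one per arm. Completers after 10% loss: 30 × 0.9 = 27 per arm, where power for d = 0.7979 is 82.0%.

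**2. The two tests compared.** In a two-arm, two-time-point design the group-by-time F is the square of the t-test on change scores. Take the SD as 1 at both times:

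- error variance of change: 2(1 − rho)
- error variance of ANCOVA on T0: 1 − rho²
- ratio, change to ANCOVA: 2(1 − rho)/(1 − rho²) = 2/(1 + rho)

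The ratio is 1.54 at rho 0.3, 1.33 at 0.5 and 1.18 at 0.7.

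**3. Power at 27 per arm** (noncentral t; ANCOVA loses one degree of freedom). If d is on the post-score scale, the effective size is d/√(2(1 − rho)) for change and d/√(1 − rho²) for ANCOVA. At rho 0.3 these are 0.7979/1.183 = 0.674 and 0.7979/0.954 = 0.836. If d is on the change scale, it stays at 0.7979 for change and becomes d × √(2/(1 + rho)) for ANCOVA.

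| rho | Post-score d: change | Post-score d: ANCOVA | Change-scale d: change | Change-scale d: ANCOVA |
|---|---|---|---|---|
| 0.3 | 68.1% | 85.4% | 82.0% | 94.6% |
| 0.5 | 82.0% | 91.3% | 82.0% | 91.3% |
| 0.7 | 96.0% | 98.1% | 82.0% | 87.7% |

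On the post-score scale at rho 0.8 the figures are 99.5% and 99.8%. On the change scale at rho 0.9 they are 82.0% and 83.9%. With d on the post-score scale, the evaluable number per arm for 80% power is 36 against 24 (rho 0.3), 26 against 20 (0.5) and 16 against 14 (0.7).

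**4. Does conditional adjustment recover the gain?** The article states no trigger, so a stand-in was simulated: ANCOVA if the baseline t-test gives p < 0.05, otherwise change scores (100,000 trials, 27 per arm, post-score d). Power for this rule against ANCOVA in every trial was 69.5% against 84.8% (rho 0.3), 82.8% against 90.8% (0.5) and 96.3% against 97.9% (0.7). Almost none of the gain is recovered. The simulated ANCOVA figures are slightly below the table because they include chance baseline differences.

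**5. How much does the open choice matter?** Under the planned effect the two models disagree on significance in 20.6%, 11.6% and 2.7% of trials at rho 0.3, 0.5 and 0.7. Under no effect, the stand-in rule has a type I error of 4.1% to 4.7%. Always reporting the smaller of the two p-values gives 7.7%, 7.3% and 6.9%.

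**The case against.** The best defence is that the planned analysis is valid, the sample size holds on its own inputs, and the gain rests on a correlation and a scale that the article does not state. All of that stands. On the post-score scale at rho 0.7 the gain is about 2 points, and above that it is trivial. A condensed article may also leave detail to a fuller plan. Here, however, the conditional rule is itself stated, so this is a choice made and not a detail left out.

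A reader might infer several stronger points that the article does not support:

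- *Adjustment is triggered by a baseline p-value.* The article never says so. It describes a literature-based decision about whether imbalance matters, which is more discretionary than a significance screen but not the same thing.
- *Type I error is inflated.* A mechanical p < 0.05 trigger showed no inflation. Reaching about 7% to 8% requires always choosing the smaller p-value, and section 2.5 says that the statistician is blinded, which limits choosing in a favoured direction.
- *The group main effect might be taken as the treatment test, with much lower power.* The interaction term is not named, but a model for changes between and within groups, with arm and time as factors, is naturally read as group by time.
- *Multiple imputation requires ANCOVA.* It does not. A difference in mean change also has one estimate and one standard error to pool.

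**Conclusion.** The point holds as a free improvement, not as an error that invalidates the trial. The default test has 2/(1 + rho) times the error variance of ANCOVA on T0. At 27 evaluable per arm the power given up is about 17 points at rho 0.3, 9 at 0.5 and 2 at 0.7 if d is on the post-score scale; it is about 13, 9 and 6 points if d is on the change scale. These figures assume equal SDs at T0 and T1, a linear T0–T1 relation and 10% loss. ANCOVA had the higher power at every rho for which the two can be told apart, but the size of the gain is uncertain because rho and the scale of d are unknown. Separately, the model for the primary outcome stays open until baseline data are seen, whatever rho turns out to be.

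**What to change.** State in section 2.8 that each primary AVLT-H score will be analysed by ANCOVA of the T1 score on arm and T0 score. This applies whatever the baseline comparison or the Shapiro–Wilk test shows; without that wording, the normality switch to unadjusted rank tests would bypass the ANCOVA. Report the arm coefficient with its 95% confidence interval, pooled over the imputations. Delete the conditional-adjustment clause for the primary outcome. Keep the repeated-measures interaction, or the rank test, as a sensitivity analysis. Age may be added as a prespecified covariate but is not essential.

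This does not settle how the five AVLT-H scores are ranked or combined; the model applies to each of them. The cost is wording only, since T0 scores are already collected, and the sample size need not change.

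### For non-normal outcomes the plan joins multiple imputation to rank tests that yield one p-value per imputed data set and ignore baseline; a baseline-adjusted difference would serve better at no cost

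*Protocol article*

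**What the plan says.** All of this stands in the protocol article, section 2.8 (Data analysis), unless noted.

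- The analysis is by intention-to-treat, and "missing data will be interpolated using multiple imputation method".
- Normally distributed outcomes get a repeated-measures ANOVA, group by time (before and after treatment).
- Non-normal outcomes get a Wilcoxon signed rank test within each group, and between groups "the Mann–Whitney test will be applied to compare the effect between groups at each time point".
- A generalized linear model is mentioned as something to be considered for non-normal data. Covariance analysis is held in reserve for baseline imbalance judged to matter.
- LTP-like plasticity, a secondary outcome, gets a repeated-measures ANOVA over four time points.
- Section 2.4 (Sample size) expects some loss: the plan will "increase the inclusion number by 10% to compensate for possible patient shedding". Section 2.7.1 describes the primary outcome, AVLT-H, as built on a 12-word list.

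**The concern.** Multiple imputation produces several completed data sets. Its usual output is a single estimate and standard error, obtained by combining one estimate and its variance from each set. The rank tests are normally reported as p-values alone, so running them as named leaves several p-values and no stated pooled quantity. An analyst who then worked from one imputed set, or averaged the imputations, would be treating imputed scores as observed, which understates uncertainty.

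The rank branch could well be used for the primary outcome. Recall of a 12-word list by people who do not meet criteria for mild cognitive impairment gives discrete scores that may sit near the ceiling.

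The between-group rank test also compares the arms at each visit separately. The T0 comparison carries no treatment effect, and the T1 comparison discards the T0 score that every participant is due to provide.

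**Working it through.** **Inputs from the article.** "levels of statistical significance will be set at *p* < 0.05" (section 2.8; two-sided assumed). "alpha and power are set at 0.05 and 80%, respectively", "with a Cohen’s effect size of *d* = 0.7979 for rTMS on the 12-word Philadelphia Verbal Learning Test" and "The final number of participants will be 30 per group" (section 2.4). 10% loss (section 2.4). Allocation 1:1 (section 2.5).

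**Assumed, not in the article.** Five imputations (m = 5), scores missing completely at random, pre–post correlation r of 0.3 or 0.6, normal or lognormal scores, and d expressed in units of the T1 standard deviation.

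**Step 1: the plan's own figure.** n per arm = 2(1.960 + 0.842)² / 0.7979² = 15.70 / 0.6366 = 24.7, so 25. The noncentral t gives 26, and 26 / 0.9 = 28.9, so 29. A Mann–Whitney calculation with asymptotic relative efficiency 0.955 gives 27, and 27 / 0.9 = 30. The stated 30 per group is reproduced and is not in question.

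**Step 2: what pools.** With estimates q and variances u from the m sets, Rubin's rules use the mean of q with total variance T = mean(u) + (1 + 1/m)B, where B is the variance of the q values between sets.

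- 2×2 ANOVA: the group-by-time F is the square of the t for the difference in mean change. A numerical check gave 0.6256 for both. It therefore has an estimate and standard error to pool.
- Generalized linear model: gives a coefficient and standard error, so it pools.
- Mann–Whitney: no pooled quantity is named, but its probability index (with a standard error) or its z can be pooled.
- Four-time-point ANOVA: a 3-df interaction F, for which multi-df pooling rules exist.

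**Step 3: type I error with no treatment effect.** 30 per arm, T1 imputed from T0 and arm by proper Bayesian regression, m = 5. There were 6,000 runs per setting (Monte Carlo standard error about 0.3 points). Ranges run over r and score distribution.

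| Use of the imputed sets | 10% missing | 20% missing (assumed) |
|---|---|---|
| Mann–Whitney, one set | 6.4–7.7% | 8.4–9.5% |
| Mann–Whitney, averaged values | 6.7–9.0% | 9.0–12.1% |
| Mann–Whitney, median p | 5.4–6.9% | 7.1–7.7% |
| Mann–Whitney, mean p | 4.2–5.6% | 5.2–5.6% |
| Mann–Whitney index, pooled | 4.1–5.2% | 4.5–5.1% |
| Mann–Whitney z, pooled | 3.3–4.5% | 3.9–4.4% |
| Baseline-adjusted difference, pooled | 4.0–5.1% | 4.4–5.1% |
| Mann–Whitney, observed data only | 4.7–5.7% | 4.7–5.1% |

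With m = 20 (10% missing, normal scores, r = 0.6), one set and averaged values each give 6.0%.

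**Step 4: power at d = 0.7979, with 27 per arm observed (30 × 0.9).**

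- Unadjusted noncentrality: 0.7979 × √(27/2) = 2.93.
- Mann–Whitney: 2.93 × √0.955 = 2.87; power ≈ Φ(2.87 − 2.01) ≈ 80%.
- Baseline-adjusted, r = 0.6: 2.93 / √(1 − 0.36) = 3.66; power ≈ Φ(3.66 − 2.01) ≈ 95%.
- Baseline-adjusted, r = 0.3: 2.93 / √(1 − 0.09) = 3.07; power ≈ Φ(3.07 − 2.01) ≈ 86%.

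Simulation with 27 per arm fully observed, r = 0.6 and no imputation gave 79.8% for Mann–Whitney and 94.6% for the adjusted model. With 10% missing and Rubin pooling, the adjusted difference had 93.5% and the pooled Mann–Whitney index 80.8%. The gap is the same size with and without imputation.

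**The case against.** The strongest reply is that the number of imputations, the imputation model and the pooling rule belong in a full protocol or analysis plan that is not shown, so their absence from an article is no error. That stands. So does the fact that one sentence there could make the named rank tests work, because the pooled index and pooled z both keep type I error at about 5% or below.

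A reader might infer more than the article supports:

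- *The rank tests cannot be pooled, so the plan has no valid intention-to-treat result.* Step 2 shows otherwise. The planned test for normal AVLT-H scores and the optional generalized linear model also pool directly.
- *The plan will inflate the type I error.* The article does not say that one set is used, that values are averaged or that the smallest p-value is taken. The word for filling in missing values is loose, but the same sentence names multiple imputation. Nor does every shortcut inflate: the mean p-value stays at 4.2–5.6% with 10% missing.
- *Imputation costs the rank test its power.* Step 4 shows the gap without any imputation.

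It can also be said that the article already offers covariance analysis. It does so only where imbalance is judged to matter, so adjustment is not assured. The generalized linear model is likewise only to be considered, alongside the rank tests.

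**Conclusion.** The point holds in limited form. For non-normal outcomes the article pairs multiple imputation with tests that, as named, deliver one p-value per imputed set and leave baseline out of the between-group comparison. This is an avoidable weakness, not a plan that cannot be carried out.

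The type I error risk is conditional: roughly 6–9% at the plan's own 10% loss if one imputed set or averaged imputations were used, under the assumed m = 5 and missingness completely at random. It would be larger at 20% missing.

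The firmer gain is from baseline adjustment. It holds type I error at about 5% for normal and for lognormal scores, and raises power from about 80% to about 94% at d = 0.7979 if r = 0.6, or to about 86% if r = 0.3. The sample size is unaffected. The four-time-point F test bears only on the secondary plasticity outcome.

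**What to change.** In section 2.8, before unblinding:

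1. Define the primary intention-to-treat result as the between-arm difference in T1 AVLT-H adjusted for T0, whether or not the scores look normal or the arms look balanced at baseline. Either pool it by Rubin's rules with an imputation model containing arm and T0, or fit it to observed data and keep imputation as a sensitivity analysis.
2. Run the rank tests on observed data only, as sensitivity analyses.
3. For plasticity, either state a multi-df pooling rule for the F test or replace it with a single contrast, such as the mean of the 5, 10 and 30 min values.

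The cost is a few sentences and a few lines of code. No extra participants, visits or measurements are needed.

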**Methods:**

In our randomized, sham-controlled trial, patients (*n* = 60) with SCD will receive 20 sessions (5 consecutive days per week for 4 weeks) of real rTMS (*n* = 30) or sham rTMS (*n* = 30) over the left DLPFC. The primary outcome is the Auditory Verbal Learning Test-Huashan version (AVLT-H). Other neuropsychological examinations and the long-term potentiation (LTP)-like cortical plasticity evaluation serve as the secondary outcomes. These outcomes will be assessed before and at the end of the intervention.

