It is suggested that impairment to synaptic plasticity plays a crucial role in the development and progression of AD (Walsh and Selkoe, 2004; Shankar et al., 2008). According to Mecca et al. (2020) [^11^C]UCB-J PET technology demonstrated significant synaptic loss caused by AD at neocortical areas such as frontal regions. Another study suggest that cerebellar LTP-like cortical plasticity mechanisms are impaired in AD (Di Lorenzo et al., 2020a). Since the discovery of SCD, neuropathological abnormalities in amyloidosis (e.g., reductions in Aβ42 and increases in amyloid tracer uptake) and neurodegeneration have appeared. The latter includes atrophy in the medial temporal lobes and paralimbic and temporoparietal cortices (Rabin et al., 2017). The loss of long-term EM has not only been referred to as merely local damage to the medial temporal lobes, but also to the malfunction of cortical plasticity on the basis of memory processes (Vidal-Piñeiro et al., 2014). Considering the precocious impairment of plasticity mechanisms in AD, researching synaptic mechanisms in patients who show initial signs of memory deficits can effectively identify early functional anomalies, predict disease progression and evaluate the effectiveness of treatments. We, therefore, decided to study the change in LTP-like plasticity induced by SCD treatment with TMS.

The primary objective of our study is to investigate the efficacy of rTMS on EM in patients with SCD. The Auditory Verbal Learning Test-Huashan version (AVLT-H) will be used as the primary outcome measure. We also explore changes in the both neural and behavioral effects (other cognitive domains) after rTMS interventions. The predictive role of the LTP-like plasticity on cognitive improvement in rTMS-treated SCD patients will be studied. We hypothesized that stimulating the left-DLPFC (l-DLPFC) with 10 Hz rTMS can produce beneficial effects on EM in SCD by enhancing LTP-like plasticity.

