## 2. Materials and methods

### 2.1. Study design

This is a randomized, double-blind, sham-controlled clinical trial, based on the Consolidated Standards of Reporting Trials (CONSORT) statement for non-pharmacologic therapy (Boutron et al., 2008). This study protocol was prepared in accordance with the Standard Protocol Items for Randomized Trials (SPIRIT) statement (Chan et al., 2015). The study was approved by the Human Research Ethics Committee at our hospital (No. 2023-002-01) and was registered with the Chinese Clinical Trial Registry (ChiCTR2300075517). Figure 1 shows details of the study design. Baseline (T0) assessments will assess demographic, behavioral, neurophysiological, and neuroimaging indicators and, following completion of the intervention program (T1), instantaneous outcomes will be measured and compared between the two groups. Patients will undergo a comprehensive clinical investigation including a medical history and a thorough neuropsychiatric assessment exploring cognitive domains (e.g., global cognitive function, language function, executive function, memory, and attention), neuroelectrophysiological examination via TMS before and after completion of the procedure. Cognitive tests and TMS test will be performed in the morning and afternoon on the same day, respectively.

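### The LTP-like plasticity model names no visit and does not combine T0 with T1, so it does not specify a test of treatment-induced change

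*Protocol article*

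**What the plan says.** The end of the Introduction gives the aim: the authors "decided to study the change in LTP-like plasticity induced by SCD treatment with TMS". The hypothesis that follows is that rTMS benefits episodic memory by enhancing this plasticity.

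Section 2.1 schedules "neuroelectrophysiological examination via TMS before and after completion of the procedure", and the abstract says of the primary and secondary outcomes: "These outcomes will be assessed before and at the end of the intervention". Within each session, section 2.7.2 records "two baselines before and 5, 10, and 30 min after the intermittent theta burst stimulation (iTBS) protocol".

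Section 2.8 first sets out a general repeated-measures ANOVA with factors "group: real vs. sham rTMS) (time: pre-vs. post-treatment" and does not list the outcomes it covers. A separate sentence then introduces the plasticity model: "In addition, we also aim to use a repeated-measures ANOVA to examine LTP-like plasticity". Its outcome and levels are "LTP-like plasticity as a function of percent change at four time points (last baseline, 5, 10, and 30 min after iTBS", and the comparison is between the two arms. The sentence names neither a visit nor the percent-change reference. The paragraph also says: "The generalized linear model (GLM) will be considered if the data is not normally distributed". Covariance analysis on baseline data is foreseen only where an imbalance is judged to affect the results.

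**The concern.** A treatment-induced change in plasticity needs either T1 compared between arms, preferably given T0, or an arm-by-visit contrast. The only model written for this outcome has arm and minutes after iTBS. The same sentence could be applied to T1 data, T0 data or both visits together, and these answer different questions.

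Two further features make the result hard to read. A baseline level expressed as percent change from itself carries no information, but it changes what the arm-by-time interaction tests. And the fallback for non-normal data is named without any provision for repeated values in the same person.

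This is a secondary outcome, but it carries the trial's mechanistic hypothesis and its claim about predicting cognitive improvement.

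**Working it through.** **Inputs.** From the protocol: 30 per arm, 1:1 allocation, alpha 0.05, four within-session levels, sessions at T0 and T1. The protocol gives no effect size or correlation for plasticity. I therefore assume d = 0.7979 at T1 (borrowed from the memory outcome in section 2.4), a T0–T1 correlation r of 0.2 to 0.7, and a common correlation ρ among the three post-iTBS values.

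**The plan's own figure.** No sample size is stated for plasticity. For the primary outcome, d = 0.7979 with two-sided alpha 0.05 and 80% power needs 26 per arm (exact t). Then 26/0.9 = 28.9, so 29 against the stated 30. The figure reproduces closely and serves here only as n.

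**1. Which visits enter.** Let d be the standardised arm difference at T1, with none expected at T0. The effective standardised effects are:
- T1 alone: d = 0.798.
- Change (arm by visit): d/√(2(1−r)), from 0.631 at r = 0.2 to 1.030 at r = 0.7.
- T1 adjusted for T0: d/√(1−r²), from 0.814 to 1.117.
- Average of both visits: (d/2)/√((1+r)/2), from 0.515 to 0.433.

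Power with 30 per arm:

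| Analysis | r = 0.2 | 0.3 | 0.5 | 0.7 |
|---|---|---|---|---|
| T1 alone | 0.86 | 0.86 | 0.86 | 0.86 |
| Change | 0.67 | 0.73 | 0.86 | 0.98 |
| T1 adjusted for T0 | 0.87 | 0.89 | 0.94 | 0.99 |
| Average of T0 and T1 | 0.50 | 0.47 | 0.42 | 0.38 |

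T0 alone gives 0.05, since no treatment has yet been given. With d = 0.5, T1 alone has power 0.48, and T1 adjusted for T0 has 0.49 to 0.76.

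**2. The baseline level, if it is the reference.** Every participant then has the same value there (0%, or 100% if expressed as a ratio).

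*Arm main effect.* With that level at 0, each person's mean over four levels is 3/4 of the mean over three. The estimate and its standard error shrink by the same factor, so F is unchanged. In simulation it was identical in every run.

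*Arm-by-time interaction.* A uniform arm difference δ after iTBS becomes the profile (0, δ, δ, δ), which is not parallel. With δ = 0.6 SD, 30 per arm and 5,000 runs per setting, the interaction was significant in 58%, 65% and 69% of runs at ρ = 0.3, 0.5 and 0.7. Without the baseline level it was significant in about 5%.

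*Sphericity.* The within-person contrast variances are (1−ρ), (1−ρ) and (1+2ρ)/4, so ε = (sum)²/(3 × sum of squares). At ρ = 0.9 they are 0.1, 0.1 and 0.7, giving ε = 0.81/1.53 = 0.53. At ρ = 0.5 all are 0.5 and ε = 1. Null rejection rates of the uncorrected interaction test, over repeated simulations:

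| ρ | ε | Type I error |
|---|---|---|
| 0.3 to 0.6 | 0.95 to 1.00 | about 5% |
| 0.7 | 0.89 | 5.5–5.7% |
| 0.8 | 0.73 | 6.3–6.7% |
| 0.9 | 0.53 | 8.3–8.8% |

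A Greenhouse–Geisser correction brings the last three rows back to about 5%.

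**3. The fallback, if it treats the three post-iTBS values as independent.** The variance of the arm difference is understated by the factor 1 + 2ρ, so type I error is about 2Φ(−1.96/√(1+2ρ)): 12%, 17%, 21% and 24% at ρ = 0.3, 0.5, 0.7 and 0.9. Simulation with 30 per arm agrees to within about one percentage point.

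**The case against.** The strongest reply is that nothing is invalid. Section 2.1 says outcomes at T1 will be compared between the groups, and under randomisation the stated model run on T1 data is a sound test of an rTMS effect. At low T0–T1 correlation, adjusting for T0 gains little (0.87 against 0.86 at r = 0.2). This stands. A reader might infer that the model cannot test whether rTMS changed plasticity, and the documents do not support that.

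The general pre/post ANOVA excludes no outcome, so it may be meant to cover plasticity as well. That reading is possible. But the plasticity model is introduced as an addition, and the protocol does not say how several within-session values become one pre and one post value.

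Other strong readings also go beyond the text:
- Pooling of visits is nowhere proposed. It is only something the wording does not rule out.
- A constant baseline level is inferred. If the first baseline or the mean of both is the reference, the last baseline varies, within the limit set by the 15% stability rule.
- The 3/4 factor changes the reported main-effect estimate but not its test.
- The type I inflation needs correlations of about 0.7 or more and no sphericity correction. The article is silent on both, and the correction is commonly left to an analysis plan.
- The generalised linear model is only to be considered, and no covariance structure is given. Independence is a risk of the wording, not a statement in it.

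**Conclusion.** The point holds as a mismatch between aim and model. Plasticity is measured at both visits to study treatment-induced change, and the model written for it neither names a visit nor uses the two together. This is more than omitted detail, because the article does specify a model, and a better one is available from data already planned.

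Under the assumed d = 0.7979 and r of 0.2 to 0.7, adjusting T1 for T0 raises power from 0.86 to between 0.87 and 0.99. Averaging visits would lower it to between 0.50 and 0.38. These figures rest on values the protocol does not give for plasticity.

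The remaining parts are conditional. If the last baseline is the reference, a significant arm-by-time interaction cannot be read as a different time course, and the uncorrected test is mildly to moderately liberal at high correlation. If the fallback ignores within-person correlation, the arm test is seriously liberal. The primary outcome is not affected. The change should be made, but it is not critical to the trial.

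**What to change.** In section 2.8:

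1. Name the plasticity test: the arm difference at T1 in percent change over 5, 10 and 30 min after iTBS, adjusted for the corresponding T0 value whether or not baseline imbalance is observed.
2. State the reference for percent change, and remove the baseline from the outcome levels. If the time course is of interest, test arm by time over the three post-iTBS levels only, with a sphericity correction or a mixed model.
3. For non-normal data, replace the generalised linear model with one that keeps within-person correlation (mixed model or GEE).

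A log-ratio scale and a reference averaged over both baseline blocks are reasonable options but not required.

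Cost: analysis wording only. All measurements are already scheduled, so no visit, participant or procedure is added.
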